#### All-cause mortality at one year

Deaths are identified on the SAE form. If a participant has death indicated on an SAE form via the 'death' variable then they will be termed "dead". Participants which do not fulfil this criteria will be termed "alive".

If a participant is "dead" then their time till death will be defined as the number of days from the date of randomisation till the date death. If the time till death is  $\leq 365$  days then the question "All-cause mortality occurred by one year?" is termed "yes". If the time till death is  $> 365$  days then the question "All-cause mortality occurred by one year?" is termed "no".

If a participant is "alive" then their time till censoring will be the number of days from the date of randomisation to the date last known to be alive. This will be determined by the completion date of the most recent trial form received. If the censored time is  $> 365$  then the question "All-cause mortality occurred by one year?" is answered "no". If the censored time  $\leq 365$  days but the follow-up CRF has been completed within the window of assessment (no earlier than 351 days from randomisation) then "All-cause mortality occurred by one year?" is answered "no". If the censored time is  $\leq 365$  and the 12-month follow-up CRF has not been returned within the scheduled window of assessment then there is not complete information regarding mortality within 1 year for this participant. Therefore, the answer to "All-cause mortality occurred by one year?" is considered to be missing.

Liver-related mortality and cardiovascular mortality will be derived in a similar fashion. Deaths of these types will be classified and indicated on the database following review of the SAE information provided by the chief investigator.

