### 5.4. Definition of adherence

Adherence to allocated intervention will be monitored via a participant's medical notes. In particular, in the carvedilol arm, participants will be asked about adherence with their trial medication at each follow-up visit and their response documented in the medical notes and subsequently transcribed onto the Follow-Up CRFs. Adherence to variceal band ligation will be documented on the Follow-Up CRFs using information available in the participant's medical notes.

We will define adherence as follows:

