#### Transplant free survival at one year

Liver transplants are identified on the SAE form. If a participant has a liver transplant indicated via the CTCAE category on the SAE form then the participant is termed as having "had a liver transplant". Participants which do not fulfil this criteria will be termed as having "not had a liver transplant".

If a participant has "had a liver transplant" then their time till transplant will be defined as the number of days from the date of randomisation till the date of transplant (indicated by the date of onset on the SAE form). If the time till transplant is  $\leq 365$  days the question "Transplant free survival at 1 year?" is answered "no". If the time till transplant is  $> 365$  the question

"Transplant free survival at 1 year?" is answered "yes".

If a participant is "transplant free" then their time till transplant will be the number of days from the date of randomisation to the date last known to be transplant free. This will be determined by the completion date of the most recent trial form received. If the censored time is  $> 365$  then the question "Transplant free survival at 1 year?" is answered "yes". If the censored time  $\leq 365$  days but the follow-up CRF has been completed within the window of assessment (no earlier than 351 days from randomisation) then "Transplant free survival at 1 year?" is still answered "yes". If the censored time is  $\leq 365$  and the 12-month follow-up CRF has not been returned then there is not complete information regarding transplant free survival within 1 year for this participant. Therefore, the answer to "Transplant free survival at 1 year?" is considered to be missing.

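### One-year survival and transplant status are dated by when a form was completed, so a participant last observed before day 351 can be scored event-free instead of missing

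*SAP*

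**What the plan says.** In SAP section 9.4, under all-cause mortality, a participant with no death on an SAE form is treated as alive, and the censoring time is "the number of days from the date of randomisation to the date last known to be alive". The next sentence fixes that date: "This will be determined by the completion date of the most recent trial form received". Three outcomes follow:

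- A censored time above 365 days is scored as no death.
- A censored time of 365 days or less is also scored as no death if "the follow-up CRF has been completed within the window of assessment (no earlier than 351 days from randomisation").
- If the time is 365 days or less and no 12-month CRF came back in the window, the outcome is missing.

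The transplant-free survival derivation follows the same pattern, using "the date last known to be transplant free. This will be determined by the completion date of the most recent trial form received". The time-to-first-bleed derivation in 9.4 also takes its last known date from form completion.

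Other parts of the SAP bear on this:

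- Section 5.4 says that carvedilol adherence responses are "documented in the medical notes and subsequently transcribed onto the Follow-Up CRFs". Banding adherence is also entered from the notes.
- Appendix C allows the 12-month visit two months either side of the target.
- Section 9.6 restricts secondary outcomes to participants who reached, and gave data for, the time point.
- Section 9.10 confines sensitivity analyses to the primary outcome.

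**The concern.** The SAP names the right quantity and then substitutes one that can be later. A completion date shows when a form was filled in. It shows that the participant was alive on that day only if the form rests on contact, or on a status check, made then. No such condition is stated, and any type of form qualifies.

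Where completion lags behind observation, unknown one-year status becomes event-free status. The missing category in 9.4 is then bypassed, as is the restriction in 9.6. Any death or transplant in the unobserved gap that never reached an SAE form is scored as a non-event. All-cause mortality is an important secondary outcome, and no sensitivity analysis would reveal the effect.

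**Working it through.** The SAP gives no figure for form lag or for mortality in this trial, so there is nothing of its own to reproduce on this point. The check applies the rule to example dates and then sizes the effect under stated assumptions.

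**Inputs from the SAP.** One year is 365 days (9.4). The early-form allowance starts at day 351 (9.4). The 12-month visit window is ± 2 months, about day 304 to day 426, or 122 days (Appendix C). Expected loss is 10% of 2630, or 263 participants (4.7).

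**Assumptions.** Visits are uniform over the 122 days. Every form has the same lag L of 14 or 30 days. Annual mortality m is 5 to 20% with constant hazard. No death in the gap reaches an SAE form.

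**Step 1: apply the rule (no death or transplant reported).**

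| Last observed | Form completed | Scored under 9.4 | Unobserved to day 365 |
|---|---|---|---|
| day 310 | follow-up CRF, day 370 | event-free (370 > 365) | 55 days |
| day 310 | follow-up CRF, day 352 | event-free (day-351 allowance) | 55 days |
| about month 6 | any form after day 365 | event-free | about 180 days |
| day 351 | follow-up CRF, day 351 | event-free (day-351 allowance) | 14 days |

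Dated by last observation, the first three would be missing for mortality. For transplant the missing branch is worded only for a 12-month CRF that was not returned, so a returned form that reflects an early visit falls under no branch. The fourth row stays event-free either way.

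**Step 2: share affected.** Those whose score changes were observed before day 351 and had the CRF completed on or after it. The share is L/122: 14/122 = 11.5% and 30/122 = 24.6%.

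Participants seen by day 365 with a form after day 365 make up the same proportions, but they must not be added. At L = 14 all of them were seen on days 351 to 365 and keep their score. At L = 30, 14/122 = 11.5% keep it, and the other 16/122 = 13.1% are already in the group that changes.

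**Step 3: understated mortality.** For a gap of g days, P(death) = 1 − (1 − m)^(g/365).

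- L = 14: gaps run from 14 to 28 days (mean 21). P is 0.295% at m = 5% and 1.275% at m = 20%. Multiplied by 0.1148, this is 0.03 to 0.15 points.
- L = 30: gaps run from 14 to 44 days (mean 29). P is 0.407% and 1.756%. Multiplied by 0.2459, this is 0.10 to 0.43 points.

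**Step 4: participants lost earlier.** Suppose all 263 expected losses were last seen near month 6 (g = 183) and each had a form dated after day 365. P is 2.54% at m = 5% and 10.58% at m = 20%. That gives 6.7 to 27.8 unseen deaths, or 0.25 to 1.06 points of 2630. This is an extreme case.

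**Step 5: treatment contrast.** Take 10% true mortality in both arms and the month-6 case. If 10% of each arm is affected, both arms record 9.5% and the risk ratio is 1.0. If 0% of one arm and 10% of the other are affected, recorded mortality is 10.0% against 9.5%, a ratio of 0.95.

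**The case against.** The strongest reply is that the document proves no lag. Section 5.4 concerns adherence items only and states no interval, so transcription could happen on the same day. How completion date is defined may sit in CRF guidance that is not shown. A form filled from the notes may also reflect what the notes show on that later day. All of this stands, and it is why the size can be given only under assumptions. It does not rescue the rule, which neither requires a status check on the completion date nor limits which forms count.

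A reader might infer that deaths and transplants after loss of contact are hidden in general. The SAP does not support that: an event on an SAE form is counted by its own date, whenever the last form was completed. Nor is everyone unobserved at day 365 scored event-free. A participant whose latest form is dated by day 365, and who has no 12-month CRF, is set to missing. A reader might also infer a biased comparison between arms. Nothing in the SAP suggests that lag differs by arm, and equal lag leaves the ratio at 1.0 in step 5.

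The last objection concerns the remedy. If every form completed without contact were discarded, 11.5 to 24.6% of survivors could become missing while all reported deaths stayed in. True mortality of 10% would then read as 0.10/(0.10 + 0.90 × 0.885) = 11.2% to 0.10/(0.10 + 0.90 × 0.754) = 12.8%, a larger error than the one being removed. This stands, and it shapes the fix.

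**Conclusion.** The point holds as a defect in the derivation rule. A participant without a reported event who was last observed before day 351 can be scored alive or transplant-free at one year because a form was completed late. For mortality, the SAP's own logic would make that participant missing.

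The likely effect is small: about 0.03 to 0.43 percentage points of understated mortality. That rests on uniform visits, a universal lag of 14 to 30 days, 5 to 20% annual mortality, and no gap death reaching an SAE form. If forms are completed at the visit, it is close to nil. It approaches one point only if most participants lost around month 6 have forms dated after day 365 and mortality is at the top of the assumed range. The primary outcome is not touched by this rule. The change is still worth making, because it is cheap, mortality matters, and the result would no longer depend on a lag that nobody has specified.

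**What to change.** In the mortality and transplant derivations of 9.4, replace the clause "determined by the completion date of the most recent trial form received" with wording such as: *the latest date on which the participant was documented to be alive (or transplant-free), by patient contact or by a documented check of records or vital status, as recorded on any form*. Then:

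- apply the day-351 and day-365 tests to that date;
- word the missing branch identically for mortality and transplant;
- align the censoring date for time to first variceal bleed, using the date last documented free of bleeding;
- reconcile the day-351 limit, which 9.4 calls the window of assessment, with the ± 2 months in Appendix C.

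The cost is about one sentence per derivation and a different date variable in the programming, which the forms must capture if they do not already. Some participants without a reported event will become missing, and their number should be reported by arm. A documented records check must count as confirmation, so that survivors are not removed needlessly while deaths remain.

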#### **Primary outcome measure**

The primary outcome measure for the comparison of carvedilol vs. variceal band ligation is variceal bleeding within 1 year of randomisation. We will define 1 year to be 365 days.

Variceal bleeding events are identified on the 6 month and 12 month follow-up forms. If a participant has at least one episode of variceal bleeding (including banding-related bleeding) indicated on either of these follow-up forms then they have “experienced variceal bleeding”. Participants which do not fulfil this criteria for experiencing variceal bleeding will be termed “free from variceal bleeding”.

For the primary outcome analysis, if a participant has “experienced variceal bleeding” and the date of onset of the first episode of bleeding as indicated on the follow-up form is within 365 days of the date of randomisation then the question “Has variceal bleeding occurred within 1 year of randomisation?” will be answered “yes”. Otherwise, it will be answered “no”. This will form the primary binary outcome.

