#### EQ-5D-5L

EQ-5D-5L is a 6-item questionnaire consisting of five multiple-choice questions and one visual analogue scale. The five multiple-choice questions concern different aspects of health (mobility, self-care, usual activities, pain/discomfort and anxiety/depression) and each require the participant to select one of five ordered responses to indicate their level of problems with each aspect. The permitted responses are chosen from one of the following: no problems=1, slight problems=2, moderate problem=3, severe problems=4, extreme problems/unable to perform activity=5. The numbers assigned to each state are then converted using the official scoring method to obtain a score. The numbers 1-5 assigned to each state have no arithmetic properties and will not be used as cardinal scores themselves. The visual analogue scale is numbered from 0 to 100, where 0 indicates the worst health a participant can imagine and 100 indicates the best health a participant can imagine. Higher scores are better for both the multiple-choice final score and the visual analogue scale. Due to the subjective nature of a questionnaire, EQ-5D responses outside of the scheduled window of assessment ( $\pm 2$  months) will be removed in a sensitivity analysis.

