## **9.6. Analysis methods – secondary outcomes**

The secondary outcomes for the trial include continuous, categorical and time-to-event data

items. The analysis population for these outcomes will be restricted to those participants who have reached and provided data for the time point of interest.

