#### *Mortality at one year*

For all-cause mortality, the number and percentage of participants who have died within one year of randomisation will be reported by treatment group. An adjusted risk ratio and 95% confidence interval will be estimated from a log-binomial regression model. Risk difference will also be reported. Liver-related mortality and cardiovascular mortality will be analysed in the same way.

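### The one-year mortality rule counts every recorded death but drops participants with partial event-free follow-up, and its day-351 window contradicts the ±2 months given elsewhere in the SAP

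*SAP*

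**What the plan says.** Section 9.4, under the primary outcome, sets the horizon: "We will define 1 year to be 365 days". The paragraph on all-cause mortality then treats the two outcomes differently.

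- **Deaths.** "Deaths are identified on the SAE form". A death at or before day 365 is coded yes. No follow-up form is required.
- **No recorded death.** The participant is termed alive and given a last-known-alive date: "This will be determined by the completion date of the most recent trial form received". The answer is no if that date is after day 365, or if the follow-up CRF was completed inside a window described as "no earlier than 351 days from randomisation".
- **Otherwise**, if the 12-month CRF did not come back within the scheduled window, "then there is not complete information regarding mortality within 1 year for this participant", and the value is missing.

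Liver-related and cardiovascular mortality are derived in a similar way. Transplant-free survival repeats the day-351 limit.

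For the analysis, section 9.6 says that the secondary-outcome population is "restricted to those participants who have reached and provided data for the time point of interest". For mortality, "An adjusted risk ratio and 95% confidence interval will be estimated from a log-binomial regression model", together with a risk difference. Section 9.10 confines sensitivity analyses to the primary outcome.

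**The concern.** Whether a participant is analysed depends on the recorded outcome. Recorded deaths stay in the numerator regardless of follow-up, while incomplete event-free follow-up leaves the denominator. A binary risk ratio cannot use the months that such a participant was known to be alive, although the SAP has already derived the date.

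The windows also disagree. A 12-month form at days 304 to 350 is on schedule in Appendix C but too early for the mortality rule, so two statisticians could code the same participant differently.

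At stake are the mortality percentages in each arm, their cause-specific versions and, if form return or visit timing differs between arms, the treatment comparison. Such a difference is possible: the trial is open-label, and section 4.2 gives the banding arm repeated endoscopies while the carvedilol arm has a four-week clinic visit and no routine endoscopic surveillance. The SAP gives no figures on it.

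**Working it through.** **1. The windows side by side**

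| Place in SAP | Window for the 12-month assessment |
|---|---|
| 9.4 mortality, rule for coding no | day 351 onward |
| 9.4 mortality, rule for missing | the scheduled window, with no number given |
| 9.4 transplant-free survival | day 351 onward to code yes; missing only if the 12-month CRF was not returned |
| 9.4 EQ-5D-5L ("EQ-5D responses outside of the scheduled window of assessment") | ±2 months |
| Appendix C | 12 months ±2 months |

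Two months either side runs from 365.25 × 10/12 = day 304 to 365.25 × 14/12 = day 426. Take a survivor whose last form is the 12-month CRF at day 330. If the scheduled window means day 351 onward, mortality is missing. If it means ±2 months, the participant meets neither the rule for no nor the rule for missing. For transplant-free survival the form was returned, so again neither rule applies.

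**2. Inputs**

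The SAP states no mortality rate, so there is no mortality figure to reproduce. Section 4.7 supplies 10% attrition and 1315 per group. Its 2362 evaluable participants (1181 per group) reproduce for 12% vs 8% at 90% power, and 2362/0.90 gives 2625 against the stated 2630. True mortality p (5% to 20%) and the share m of survivors set to missing are assumptions.

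**3. Reported mortality if SAE forms capture every death**

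Reported = p / [p + (1 − p)(1 − m)]. With m = 10%:

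| True p | Calculation | Reported |
|---|---|---|
| 5% | 0.05/0.905 | 5.5% |
| 10% | 0.10/0.910 | 11.0% |
| 15% | 0.15/0.915 | 16.4% |
| 20% | 0.20/0.920 | 21.7% |

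**4. If deaths after loss are not recorded**

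Take constant, independent hazards giving 10% mortality and 10% loss over the year: λ = c = −ln 0.9. Recorded deaths are ½(1 − 0.81) = 0.095, and participants alive and still followed are 0.81. Reported mortality is 0.095/0.905 = 10.5%, about half the excess in step 3.

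If the hazard after loss is twice as high, true mortality is 10.5% against 10.5% reported. If it is three times as high, the truth is 10.9% against 10.5%, and the bias has reversed.

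**5. The risk ratio (all deaths captured)**

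- Equal missingness of 10%, true risks 8% vs 10% (ratio 0.80): (0.08/0.908)/(0.10/0.910) = 0.802.
- No true effect, p = 10%, survivors missing 5% vs 15%: 0.10/0.955 = 10.5% vs 0.10/0.865 = 11.6%. The ratio is 0.91, or 1.10 the other way round. With 1315 per arm randomised, the expected difference is 0.0109 with standard error 0.0128, so a nominal 5% test rejects in about 14% of trials.

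**6. What Kaplan-Meier would give**

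Take 1000 participants and 100 deaths spread evenly and all captured, with 90 of the 900 survivors last seen mid-year. Survival is 0.95 × (1 − 50/860) = 0.895, so mortality is 10.5%, against 11.0% under the SAP rule and a true 10%. Counting everyone without a recorded death as alive gives 100/1000 = 10%, exact when capture is complete.

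**The case against.** Several stronger readings are tempting, and the SAP does not support them.

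- **That only true survivors can be missing, so mortality must be inflated.** The rule terms alive anyone without a death on an SAE form. Someone who is lost and later dies unreported is therefore also set to missing. Step 4 shows that the direction is then not certain.
- **That the inflation is large.** If 12-month visits were spread evenly over days 304 to 426, 47/122 = 39% would fall before day 351. With 10% attrition added, 10% would be reported as 16.7%. No document gives a visit distribution, visits are likely to cluster near the 12-month target, and any trial form dated after day 365 also codes the participant as no. If visits centred on day 365 with a standard deviation of 14 days (also an assumption), about 16% would fall before day 351.
- **That the risk ratio is biased in any case.** With equal missingness it barely moves, and the 5% vs 15% split is illustrative.
- **That section 9.6 removes deaths.** Section 9.4 codes a recorded death as yes, so that participant has provided data.
- **That the censoring time is never used.** It is used to classify participants, though not in any time-to-event analysis.

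It can also be said that a binary one-year outcome on received data is a legitimate pre-specified choice, and that Kaplan-Meier keeps part of the asymmetry if deaths reported after the last form still count. Both points stand. Neither removes the exclusion by recorded outcome or the conflict between windows, and no planned sensitivity analysis would show their effect on mortality.

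**Conclusion.** The concern holds in limited form. The rule makes exclusion depend on the recorded outcome, and its window contradicts two other places in the SAP, leaving some on-schedule participants missing or unclassifiable.

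The likely size is modest. At an assumed 10% mortality and 10% of survivors missing, about 11.0% is reported if death capture is complete and about 10.5% if deaths after loss are unrecorded and loss is independent. There is no excess, or a deficit, if mortality after loss is two to three times higher. A material effect on the risk ratio needs missingness that differs by arm, for which the SAP offers no evidence either way.

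The primary outcome and its sample size do not use this rule. Should-fix, before database lock.

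**What to change.** 1. State one 12-month window and use it in the mortality, transplant-free survival and EQ-5D-5L paragraphs of 9.4 and in Appendix C. Classify every returned form explicitly. Putting ±2 months into the existing mortality rule is not enough by itself, since it would code someone last seen at day 304 as alive at day 365.
2. Estimate day-365 mortality in all randomised participants by Kaplan-Meier, censoring at the last-known-alive date that 9.4 already derives. Use cumulative incidence for liver-related and cardiovascular death. Make this the main analysis, or at least report it beside the log-binomial risk ratio, so that partial follow-up is not discarded. It reduces the asymmetry but does not abolish it.
3. Extend 9.10 with a sensitivity analysis for missing vital status. Include a scenario that counts every randomised participant without an SAE-recorded death as alive. Section 9.10 already reasons in this way for bleeding, on the ground that an SAE form would reveal so serious an event.

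The cost is some SAP wording, a little analysis code, and a changed or additional mortality measure to report.
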